### Recruitment

Women attending a participating gynecologist are asked for their phone numbers and to consent to be contacted by the project physician. Standard information about the project has been distributed by the project physician to the gynecologists to ensure standardized information is given to women. The consent forms are sent from the gynecologists to the project physician. The consent forms are matched with new CIN2 diagnoses retrieved from the pathology register every second week [19]. If there is a match between a consent form and a CIN2 diagnosis, the gynecologist is contacted for information about the treatment plan agreed with the woman. If watchful waiting with a follow-up biopsy in 6 months is planned, the woman will be included in the project and randomized (Fig. 2). No side effects, complications, or risks are expected due to participation in the project.

**Fig. 2 Fig2:**
[figure not shown]
SPIRIT flowchart of the project design. CIN2 Cervical intraepithelial neoplasia grade 2

### Randomization

Women meeting the inclusion criteria and for whom we have received from the gynecologists a phone number and a signed consent form agreeing to be contacted are included in the study and randomized with an allocation of 1:1. The randomization sequence uses a computer-generated random number list per region, since policies for follow-ups and treatment vary slightly across the regions. Randomization is undertaken by a third person, after which the project physician contacts women randomized to the intervention group.

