### Outcome measures

#### Primary endpoint

The primary endpoint is the relative rate of CIN2 regression between women in the intervention group and women in the control group. Regression is defined as having a diagnosis < CIN2 in the follow-up biopsy. As all women have CIN2 at entry, having less than CIN2 at follow-up entails a decreased risk of conization, and the woman will be referred back to her general practitioner for less frequent follow-ups according to national guidelines [6]. This outcome is, therefore, highly desirable. Another primary endpoint is the relative rate of CIN2 regression between women who consented to condom use and women in the control group. The regression rate in women who did not consent to condom use will be used to control for a possible selection bias. Regression rates will be reported by age.

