### Data analysis plan

The relative regression rate (RRR) for CIN2 in the intention-to-treat analysis will be calculated as$$ \mathrm{RRR}=\frac{\left(\mathrm{number}<\mathrm{CIN}2\ \mathrm{at}\ \mathrm{follow}\hbox{-} \mathrm{up}\ \mathrm{in}\ \mathrm{in}\mathrm{tervention}\ \mathrm{group}\right)/\left(\mathrm{all}\ \mathrm{women}\ \mathrm{in}\ \mathrm{in}\mathrm{tervention}\ \mathrm{group}\right)}{\left(\mathrm{number}<\mathrm{CIN}2\ \mathrm{at}\ \mathrm{follow}\hbox{-} \mathrm{up}\ \mathrm{in}\ \mathrm{control}\ \mathrm{group}\right)/\left(\mathrm{all}\ \mathrm{women}\ \mathrm{in}\ \mathrm{control}\ \mathrm{group}\right)}. $$

The relative HPV-clearance rate (RCR) is calculated as$$ {\displaystyle \begin{array}{l}\mathrm{RCR}=\\ {}\frac{\left(1-\mathrm{number}\ \mathrm{HR}\hbox{-} \mathrm{HPV}+\mathrm{at}\ \mathrm{follow}\hbox{-} \mathrm{up}\ \mathrm{in}\ \mathrm{in}\mathrm{tervention}\ \mathrm{group}\right)/\left(\mathrm{number}\ \mathrm{HR}\hbox{-} \mathrm{HPV}+\mathrm{at}\ \mathrm{baseline}\ \mathrm{in}\ \mathrm{in}\mathrm{tervention}\ \mathrm{group}\right)}{\left(1-\mathrm{number}\ \mathrm{HR}\hbox{-} \mathrm{HPV}+\mathrm{at}\ \mathrm{follow}\hbox{-} \mathrm{up}\ \mathrm{in}\ \mathrm{control}\ \mathrm{group}\right)/\left(\mathrm{number}\ \mathrm{HR}\hbox{-} \mathrm{HPV}+\mathrm{at}\ \mathrm{baseline}\ \mathrm{in}\ \mathrm{control}\ \mathrm{group}\right)}.\end{array}} $$

These calculations are possible because we have a closed population, in which all women recruited are followed up for the entire observation period. Logistic regression will be used to analyze the questionnaire data as predictors of outcomes. SAS version 9.4 will be used for the analysis.

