### Strengths and limitations

A strength of this study is its design as a public health randomized controlled trial embedded in the routine treatment and follow-up program for women with cervical lesions. This gives us two groups of women who are comparable except for the intervention. It is, furthermore, a strength to have three regions included. In Denmark, health care is paid for by the government and is free of charge [26], but there are minor regional variations in clinical procedures, and recruiting participants from three regions ensures that there is a representative sample of women.

The number of drop-outs is a limitation in this project. We do not receive consent to be contacted from all women attending a gynecologist, some women in the intervention group cannot be reached by phone or text message, and some women do not want to participate. Participating women may, therefore, be a selected group. Furthermore, adherence to condom use is inevitably self-reported. This information is collected from questionnaires at the end of the project, so there could be some recall bias. A punch biopsy may alter the HPV infection, and the disappearance of a type-specific HPV infection can be caused either by a biopsy or by an actual clearance. As the study is embedded in the clinical setting, we are not able to validate histology diagnoses or perform p16 staining. However, as the routine diagnostic procedures are used for both the intervention group and the control group, any possible misclassification will affect the two groups equally.

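### Randomisation is listed separately by region, but the primary relative regression rate is a crude ratio pooled over regions: a low-severity, nearly free improvement

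*Protocol article*

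**What the plan says.** **Design.** In the Protocol article, section Randomization, eligible women "are included in the study and randomized with an allocation of 1:1". The same section adds: "The randomization sequence uses a computer-generated random number list per region, since policies for follow-ups and treatment vary slightly across the regions". Strengths and limitations repeats the reason: "there are minor regional variations in clinical procedures". Three regions take part.

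**Analysis.** The Data analysis plan section introduces the primary estimator with "The relative regression rate (RRR) for CIN2 in the intention-to-treat analysis will be calculated as" and gives a formula: women below CIN2 at follow-up divided by all women in the intervention group, over the same proportion in the control group. It has no stratum, weight or covariate. The supporting reason concerns follow-up, not region: "These calculations are possible because we have a closed population, in which all women recruited are followed up for the entire observation period".

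**Where region might otherwise enter.** The only model named is for another purpose: "Logistic regression will be used to analyze the questionnaire data as predictors of outcomes". The only planned breakdown of the outcome is in the Primary endpoint section: "Regression rates will be reported by age". Neither involves region.

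**The concern.** When a trial randomises within strata because practice is thought to differ between them, the analysis normally conditions on those strata. Here the article gives the reason for separate lists and then writes out an estimator that does not use them. This is a stated formula, not a silence that an analysis plan would be expected to fill.

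Region could plausibly matter. The endpoint is a routine local biopsy reading. The Setting section describes different pathology arrangements by region and a Capital Region contribution from private practices only. Strengths and limitations says that histology cannot be validated.

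The stake is efficiency. What a crude analysis loses depends on how the lists were built:

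- **Lists that force balance within region:** a standard unstratified standard error ignores that balance and is too large, so the test is conservative.
- **Plain random numbers:** chance imbalance between arms within a region adds avoidable scatter to the crude ratio.

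**Working it through.** **1. The plan's own sample size.** Inputs from Power calculation: 22% regression without condoms, 2.5 times that with condoms, 60% condom use, power 95%, significance level 0.05 (taken as two-sided, since the side is not stated).

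- Relative risk by intention to treat: 0.6 × 2.5 + 0.4 × 1 = 1.9, so the intervention rate is 0.22 × 1.9 = 0.418.
- n per group = [1.960 √(2 × 0.319 × 0.681) + 1.645 √(0.22 × 0.78 + 0.418 × 0.582)]² / 0.198² = (1.292 + 1.059)² / 0.0392 ≈ 141.03, rounded up to 142.

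This reproduces the stated 140 to within 2%. The rounded relative risk of 2.0 printed in that section gives 116. The check below therefore uses 1.9 and 140 per group.

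**2. Rough size of the regional component.** Assume three equal regions averaging 22%, with total variance 0.22 × 0.78 = 0.1716.

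- Rates 12/22/32%: between-region variance (0.10² + 0 + 0.10²)/3 = 0.00667, and 0.00667/0.1716 = 3.9%.
- Rates 17/22/27%: (0.05² + 0 + 0.05²)/3 = 0.00167, and 0.00167/0.1716 = 1.0%.

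**3. Direct comparison.** For region i, let a and b be the women who regress in the intervention and control arms, n1 and n0 the arm sizes, and n = n1 + n0.

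- Crude: RRR = (Σa/Σn1)/(Σb/Σn0), tested with the usual log-scale standard error √(1/A − 1/N1 + 1/B − 1/N0), where capitals are totals over regions. The article names no test, so this choice is an assumption.
- Stratified: Mantel-Haenszel RR = Σ(a·n0/n) / Σ(b·n1/n), with log-scale variance Σ(n1·n0·(a+b)/n² − a·b/n) divided by the product of those two sums.

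There were 200,000 simulated trials per scenario, with 280 women in all. The region shares of 50/35/15%, the regional control rates and a common relative risk across regions are assumptions. The control rates average about 22% in every scenario.

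| Control rates by region | Lists | Type I error, crude / stratified | Power at RR 1.9, crude / stratified | Power gain, points |
|---|---|---|---|---|
| 22/22/22% | exact balance | 4.75% / 4.70% | 94.63% / 94.63% | 0.00 |
| 22/22/22% | unblocked | 4.70% / 4.71% | 94.57% / 94.39% | −0.18 |
| 18/24/30% | exact balance | 4.65% / 4.71% | 94.76% / 94.92% | 0.16 |
| 18/24/30% | unblocked | 4.66% / 4.68% | 94.47% / 94.66% | 0.19 |
| 12/28/41% | exact balance | 4.02% / 4.71% | 95.68% / 96.73% | 1.05 |
| 12/28/41% | unblocked | 4.71% / 4.70% | 94.56% / 96.48% | 1.92 |

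**4. Reading the results.**

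- Bias: the average estimate (back-transformed from the log scale) lies between 1.913 and 1.915 for both methods in every scenario with true value 1.9.
- Exact balance: the two point estimates coincide. At 12/28/41% both have a log-scale standard deviation of 0.1820, but the mean standard error is 0.1900 crude and 0.1805 stratified. The crude test is therefore conservative.
- Unblocked lists: at 12/28/41% the estimates themselves differ in precision, with standard deviations of 0.1925 crude and 0.1839 stratified.

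**The case against.** The strongest reply is that nothing here is wrong. With 1:1 allocation inside every region, region does not confound the comparison and the crude ratio is a legitimate estimate. The article describes the variation as slight and minor, says that all women are managed under national guidelines, and nowhere reports that regression rates differ by region. The section also gives only a point-estimate formula, so any interval, test or adjustment could be in an analysis plan that is not shown. Most of this stands, and it rules out several stronger readings that a reader might infer:

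- **That the crude RRR is biased.** Neither the design nor the simulation supports this. Chance imbalance is ordinary sampling error: with unblocked lists the crude type I error was about 4.7%.
- **That regression rates vary by region.** The documents say that policies and procedures vary, and give no outcome rates by region.
- **That the benefit of separate lists is lost.** If the lists force balance, the crude estimate already benefits and only its standard error is too large. If they do not, there was little design gain to lose. The article does not say whether blocks were used, and an article may leave that out.
- **That the planned interval is too wide.** No interval is specified, so the point can only concern what an unstratified one would do.

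The reply does not remove the mismatch itself. The estimator is written out in full, and it does not carry the factor by which women were randomised.

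**Conclusion.** The mismatch is real and its consequence is small. If regional rates differ, a crude analysis is slightly conservative or slightly less precise. At a true relative risk of 1.9 the cost is about 0.1 to 0.2 points of power under 18/24/30%, and 1 to 2 points under 12/28/41%, a spread hard to square with variation called slight. If regions do not differ, stratifying gains nothing and costs at most about 0.2 points.

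These sizes rest on assumed region shares, assumed regional rates and a common relative risk. The text mismatch is certain; its practical size is not known from the documents. No conclusion, sample size or validity claim changes. This is a free improvement of low severity.

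**What to change.** State in the analysis plan that the primary intention-to-treat RRR is a Mantel-Haenszel relative risk stratified by region with its 95% confidence interval, and that the pooled ratio in the Data analysis plan section is descriptive. A log-binomial or robust-Poisson model with arm and region is an acceptable alternative. It is not the same estimator, so one of the two should be named in advance. Adding age is a separate option and is not needed here.

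The cost is one sentence. Region is known for every woman at randomisation, the method is standard in SAS, and no data or sample size change is required. By the dates in Trial status, recruitment closed on 31 January 2019 and the last follow-up diagnosis is due by 30 September 2019, so the choice can be fixed before outcomes are complete. In an unblinded trial, this also prevents a later choice between crude and stratified results.

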### Blinding

The trial is unblinded.

### Outcome measures

#### Primary endpoint

The primary endpoint is the relative rate of CIN2 regression between women in the intervention group and women in the control group. Regression is defined as having a diagnosis < CIN2 in the follow-up biopsy. As all women have CIN2 at entry, having less than CIN2 at follow-up entails a decreased risk of conization, and the woman will be referred back to her general practitioner for less frequent follow-ups according to national guidelines [6]. This outcome is, therefore, highly desirable. Another primary endpoint is the relative rate of CIN2 regression between women who consented to condom use and women in the control group. The regression rate in women who did not consent to condom use will be used to control for a possible selection bias. Regression rates will be reported by age.

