**Methods/design:**

This is a randomized clinical trial of women with CIN2. The intervention group was advised to use condoms between the date of diagnosis and the date of their follow-up visit. The control group received standard care. Cervical samples were tested for HPV. The primary endpoint will be the intention-to-treat analysis with the relative rate of CIN2 regression between the intervention group and the control group. Regression is defined as <CIN2 at the follow-up visit. In addition, a per-protocol analysis of the regression rate in women adhering to condom use compared with the control group will be performed. The secondary endpoint will be the HPV-clearance rate in the condom group.

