### Power calculation

Based on the literature [16, 17], we expect the regression rate in non-condom users to be around 22%, and regression in condom users to be 2.5 times larger. We expect the rate of condom use to be 60% in the intervention group, which gives an expected relative risk of 2.0 for the intervention group compared to the control group. With a power of 95% and a 0.05 significance level, we would need 140 women in each group.

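### A comparison of self-selected consenters with all controls is called a primary endpoint, although the abstract, the sample size and the analysis formula treat only the intention-to-treat comparison as primary

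*Protocol article*

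**What the plan says.** The Primary endpoint section opens with the randomised comparison: "The primary endpoint is the relative rate of CIN2 regression between women in the intervention group and women in the control group". It then adds a second one: "Another primary endpoint is the relative rate of CIN2 regression between women who consented to condom use and women in the control group". It also says that the regression rate of women who declined will serve to control for possible selection bias.

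The abstract (Methods/design) differs: "The primary endpoint will be the intention-to-treat analysis with the relative rate of CIN2 regression between the intervention group and the control group". It gives the other comparison as something done in addition: "a per-protocol analysis of the regression rate in women adhering to condom use compared with the control group will be performed". The label changes (primary in one place, additional in the other), and so does the population (consented in one, adhering in the other).

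The remaining sections fit a single ITT primary:

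- **Power calculation.** It sizes the whole intervention group against control, diluted for incomplete condom use: "With a power of 95% and a 0.05 significance level, we would need 140 women in each group".
- **Data analysis plan.** The relative regression rate is written out for ITT only, with all women of each group in the denominator.
- **Discussion and Perspectives.** Both link a guideline recommendation to the trial's result without saying which comparison decides.

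**The concern.** The two comparisons do not carry the same weight as evidence. ITT is protected by randomisation. The second takes the women in one arm who could be reached and who agreed after allocation (Intervention group section) and sets them against every control, none of whom was contacted (Control group section). The control arm still contains the women who would have been unreachable or would have refused. Strengths and limitations concedes that participants may be a selected group.

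If ITT is null and the consenter comparison is positive, nothing stated in the article prevents a positive conclusion from the non-randomised contrast, because it too is labelled primary. Two things are at stake: some inflation of the error rate from a second test, and, more seriously, a guideline proposal that could rest on a difference between the kinds of women compared.

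**Working it through.** **1. What the sample size covers.** The inputs come from the Power calculation: 22% regression without condoms, 2.5 times that with them, and, for uptake, "We expect the rate of condom use to be 60% in the intervention group". The article then prints a relative risk of 2.0.

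- Unrounded relative risk: 0.6 × 2.5 + 0.4 × 1 = 1.9. The intervention-arm rate is then 1.9 × 22% = 41.8%.
- Two-sided 0.05 is assumed, as the article does not state sidedness. With 95% power and the pooled-variance formula without continuity correction, the mean rate is 0.319 and n = [1.96√(2 × 0.319 × 0.681) + 1.645√(0.22 × 0.78 + 0.418 × 0.582)]² / 0.198² ≈ 141.03, so 142 per group.
- Other formulas give 138 (unpooled) and 141 (arcsine). Power at 140 per group is 94.9%.

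The stated 140 is thus reproduced to within 3%, as a calculation for ITT alone. The printed relative risk of 2.0 would give 116, so 1.9 appears to have been rounded for print. This does not affect the present point.

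**2. Error rate if either test counted, with no effect and no selection.** Let c be the share of the intervention arm that consents. The article gives no consent rate. Its 60% is the expected rate of condom use and is borrowed here as an assumption.

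Both tests share the control arm, and the consenters are part of the intervention arm, so the correlation of the two test statistics is ρ = 2 / √(2 × (1/c + 1)). For c = 0.6, ρ = 2 / √(2 × 2.667) = 0.866. Bivariate normal probabilities with critical value 1.96:

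| Consenting (assumed) | ρ | At least one significant, two-sided | At least one significant in favour of condoms |
|---|---|---|---|
| 40% | 0.76 | 8.1% | 4.0% |
| 60% | 0.87 | 7.3% | 3.7% |
| 70% | 0.91 | 7.0% | 3.5% |
| One test only | – | 5.0% | 2.5% |

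A simulation with binomial data (140 per arm, 22% regression, 1,000,000 runs) gave 7.4% and 3.8% at 60%.

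**3. Error rate with selection.** There is still no condom effect and 60% consent (84 of 140). Suppose consenters would regress at 27% anyway while the arm averages 22%. Non-consenters then regress at (0.22 − 0.6 × 0.27) / 0.4 = 14.5%. The gap of 5 points is an assumption. Simulated results:

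| Consenters' own rate (assumed) | ITT significant, two-sided | Consenter test significant, two-sided | Either test significant in favour of condoms |
|---|---|---|---|
| 22% (no selection) | 5.0% | 5.0% | 3.8% |
| 27% | 4.8% | 14% | 14% |
| 32% | 4.5% | 39% | 39% |

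With the 5-point gap and the consenting share varied from 40% to 80%, the last column runs from 12% to 15%. In the 60% rows above, the ITT test stays at about 5% or just below.

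**The case against.** The strongest reply is that the endpoint section is loosely labelled and that ITT is plainly the intended primary. It is named first, the abstract names it alone, and it is the only comparison with a formula and a sample size. Testing order and alpha allocation are commonly left to an analysis plan, and this is a condensed article. The 0.05 in the Power calculation is a design level for one comparison; it does not say that two tests share it.

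Much of this stands. A reader might infer that the trial may claim success on either test. The article contains no such rule; it only fails to exclude it, so the figures above are conditional on that reading. A reader might also infer that the false-positive rate doubles to about 10%. It does not: independent tests would give 1 − 0.95² = 9.75%, but these two are strongly correlated. The 7.3% also counts results against condoms; the excess risk of a false benefit claim without selection is about 1.2 points (3.7% − 2.5%).

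The authors also plan to use the non-consenters' rate to control for selection bias. That acknowledges the problem, but the comparison keeps its primary status. Selection could also run the other way and make false benefit claims less frequent.

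The contradiction itself remains. Which endpoint is primary is a matter for the protocol, and two sections of this article answer it differently. An analysis plan that set a testing order would still have to choose between them.

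**Conclusion.** The point holds as a stated contradiction that gives primary status to a non-randomised comparison. It should be corrected, but it does not undermine the ITT design, whose sample size is reproduced.

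Multiplicity alone is a modest problem. Selection matters more, and its size is unknown: the 14% rests on an assumed 5-point gap and an assumed 60% consenting. All the error rates assume that a significant result on either comparison would be taken as success, which the article neither states nor rules out. Independently of those figures, the article leaves open whether the second population is women who agreed to use condoms, known at enrolment, or women who used them, known only from the questionnaire at the end of the period.

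**What to change.** In the Primary endpoint section, state that the ITT relative regression rate is the only primary endpoint, tested at two-sided 0.05. Make the non-randomised comparison secondary or supportive, and say that it cannot carry the conclusion unless ITT is significant. Reconcile the abstract with the endpoint section on whether that comparison concerns women who consented or women who adhered.

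This takes a few sentences. ITT alpha, the 140 per group and the ITT power of about 95% are unchanged. Keeping both as primaries with a Bonferroni split (0.025 each) would instead lower ITT power at 140 per group to 91.0%, or need 165 per group for 95%, and would do nothing about selection. Trial status puts the last follow-up diagnosis at 30 September 2019, so on the article's timeline the change could be made and dated before the outcome data are complete.

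### The second primary endpoint compares women who consented after randomisation with the whole control group, so selection is mixed into the ratio; the abstract gives this comparison a different status and population

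*Protocol article*

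**What the plan says.** The Primary endpoint section first names the ITT comparison of the randomised groups. It then adds: "Another primary endpoint is the relative rate of CIN2 regression between women who consented to condom use and women in the control group". On selection it says: "The regression rate in women who did not consent to condom use will be used to control for a possible selection bias".

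The abstract (Methods/design) ties the primary endpoint to the ITT analysis and describes the other comparison differently: "a per-protocol analysis of the regression rate in women adhering to condom use compared with the control group will be performed".

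The Randomization and Intervention group sections fix the order of events. Women are randomised, the physician then calls those in the intervention arm, and those reached agree or decline by phone. A signed form follows for those who agree, and condoms are sent once it is returned. Women not reached after repeated attempts are treated as missing. The control group is never contacted. Follow-up diagnoses come from the pathology register for the intervention group and for the controls.

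Strengths and limitations concedes: "Participating women may, therefore, be a selected group".

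**The concern.** Consent to condom use is a post-randomisation event seen in one arm only. The consenter group leaves out women who could not be reached and women who declined. The control group still contains the counterparts of both. Randomisation therefore does not protect this ratio: it mixes any effect of the advice with differences between women who can be reached and agree and women who cannot or do not.

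Contrasting consenters with non-consenters does not separate the two, because those groups differ in selection and in treatment at once.

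The abstract and the Primary endpoint section also disagree on status (additional per-protocol analysis or primary endpoint) and on population (adhering or consented). Adherence is known only from the questionnaire at the end of the intervention period, so adherers are a further selected subset.

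At stake is a result labelled primary that could be positive without any effect, or null despite a real one.

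**Working it through.** **Inputs from the Power calculation section.** "we expect the regression rate in non-condom users to be around 22" per cent; "regression in condom users to be 2.5 times larger"; "We expect the rate of condom use to be 60% in the intervention group"; 140 women per group for 95% power at the 0.05 level.

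**The plan's own figure.** Condom users: 2.5 × 0.22 = 0.55. Intervention arm: 0.6 × 0.55 + 0.4 × 0.22 = 0.418, a relative risk of 0.418/0.22 = 1.9 (the article says 2.0). The two-sided comparison of 0.418 with 0.22 needs 142 per group with pooled variance, 138 unpooled and 141 by arcsine. Power at 140 is 94.9%. The stated 140 is thus reproduced, and it rests on the ITT contrast alone.

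**Assumptions not in the documents.** No consent share is given, so the 60% condom-use rate stands in for it. The untreated rates in consenters and non-consenters are chosen so that they average 22%.

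**Bias with no condom effect.** The naive ratio is the consenters' untreated rate divided by 0.22. False positives come from the normal approximation for a two-sided 5% test with 0.6 × 140 = 84 consenters and 140 controls.

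| Consenters / non-consenters | Average | Naive ratio | False positives | Consenter ÷ non-consenter |
|---|---|---|---|---|
| 25% / 17.5% | 0.6 × 25 + 0.4 × 17.5 = 22% | 1.14 | 8.4% | 1.43 |
| 28% / 13% | 0.6 × 28 + 0.4 × 13 = 22% | 1.27 | 17.8% | 2.15 |
| 30% / 10% | 0.6 × 30 + 0.4 × 10 = 22% | 1.36 | 27.2% | 3.00 |

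The last column lies further from 1 than the naive ratio, so contrasting the two groups makes matters worse.

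**Direction and consent share.** Let r be the consenters' untreated rate divided by the non-consenters', and c the consent share. The naive null ratio is r/(c·r + 1 − c).
- r = 0.5, c = 0.6: 0.5/0.7 = 0.71. A true ratio of 1.5 would then appear as 1.5 × 0.71 = 1.07.
- r = 1.5: from 1.25 (c = 0.4) to 1.07 (c = 0.8).
- r = 2: from 1.43 (c = 0.4) to 1.11 (c = 0.8).

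**What the non-consenters' rate can do.** Would-be consenters in the control arm have an implied rate of [control rate − (1 − c) × non-consenter rate]/c.
- 28%/13% case: (0.22 − 0.4 × 0.13)/0.6 = 0.28, so the ratio is 0.28/0.28 = 1.0. The other two rows also give 1.0.
- True ratio 2.5 and r = 1.5: non-consenters 0.22/1.3 = 0.169, untreated consenters 0.254, advised consenters 0.635. Naive ratio 0.635/0.22 = 2.89; consenter ÷ non-consenter 3.75; complier ratio 0.635/[(0.22 − 0.4 × 0.169)/0.6] = 2.5.

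**Limit of this estimate.** If allocation changes regression in non-consenters by δ, the ITT difference shifts by (1 − c)δ. The complier risk difference is then biased by (0.4/0.6)δ = 0.67δ.

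**Precision.** With 22% in all groups, the standard error of the naive risk difference is √[0.22 × 0.78 × (1/84 + 1/140)] = 0.057. That of the complier difference is √[2 × 0.22 × 0.78/140]/0.6 = 0.0825. The interval is about 1.4 times as wide.

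**The case against.** The strongest reply is that the article already recognises the problem. It plans to use the non-consenters' rate against selection bias and names no method, and a full protocol or analysis plan that is not shown may supply one. A reader might infer that the planned use of that rate fails to remove the bias. The documents do not support that: no operation is stated, and the correction worked through above uses this very rate. A missing formula is no fault in a condensed article. What stands is that the endpoint, as defined and labelled primary, is the uncorrected ratio.

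The ITT comparison is also well placed. It is listed first, it is the abstract's primary endpoint, it has an explicit formula, and it alone is powered. Nothing in the Discussion says that a guideline proposal would rest on the consenter contrast. This limits the severity but does not remove the second primary label or the conflict with the abstract.

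Finally, a reader might take the complier estimate to be valid without conditions. It is not. The Intervention group section has the physician give the advice in the call, so women who were reached and then declined may have been affected by it. The ratios of 1.0 above hold because the scenarios assume no such effect.

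**Conclusion.** The point holds in a limited form. The second primary endpoint is confounded by selection unless consenters and non-consenters share the same untreated regression rate, and the article itself doubts that participants are unselected. Its status and population conflict with the abstract.

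Under the stated assumptions, the naive ratio with no effect is 1.14 to 1.36 with about 8% to 27% false positives, or 0.71 if selection runs the other way. A reader might take these as the error rates to be expected in this trial. They are not: the documents give neither a consent share nor rates by consent status, so the figures show only what moderate selection could do, in either direction.

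This should be fixed before analysis. The randomised ITT comparison and the sample size are unaffected.

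**What to change.** 1. Keep the ITT ratio as the sole primary endpoint, and make the abstract and the Primary endpoint section agree on the status and population of the other comparison.
2. Define *consented* as one step, either the verbal agreement by phone or the returned signed form, since c depends on it.
3. Replace the naive contrast with a supportive secondary complier-average estimate: consenter rate ÷ {[control rate − (1 − c) × non-consenter rate]/c}, where c is the proportion consenting in the intervention arm and the non-consenters include unreached women. Give a bootstrap or delta-method confidence interval.
4. State what it estimates and assumes. It is the effect of the advice in consenters, not of condom use itself. It needs allocation to have no effect on non-consenters, which is doubtful for women who were advised and then declined, and near-complete follow-up in both arms.
5. Label any analysis of adherers exploratory.

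The cost is revised wording, one extra analysis program and a wider interval than the naive contrast. No new data are needed, because register outcomes are already retrieved for both arms.
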